### Operation procedure

#### Laparoscopic total gastrectomy

The laparoscopic total gastrectomy is to be carried out with endotracheal intubation under general anesthesia. The peritoneal cytology examination should be first taken after entering the abdominal cavity. After the peritoneal cytology examination, the surgeon should explore the abdominal cavity to determine if there is any regional invasion or distant metastasis, including hepatic, peritoneal, mesenteric, or pelvic metastasis. Then, total gastrectomy with D1+/D2–10 lymphadenectomy will be performed according to the Japanese Gastric Cancer Treatment Guideline (Fourth edition, May. 2014) (Table 1). If clinical stage II or more diseases are diagnosed intraoperatively, D2 radical gastrectomy should be performed, and these patients will be excluded from this study. A proximal margin of at least 2 cm is recommended for T1 tumors, 3 cm is recommended for T2 or deeper tumors with an expansive growth pattern (Bormann I and II), and 5 cm is recommended for those with infiltrative growth pattern (Bormann III and IV). It is advisable to examine the proximal resection margin by Pathological Frozen Section routinely to confirm the negative proximal resection margin during the operation. The distal margin located in the duodenal bulb. The digestive tract reconstruction methods should be determined by the doctor in charge according to their experience and the specific intraoperative circumstances. Roux-en-Y reconstruction is recommended, and the linear and circle staplers are both acceptable. The laparoscopic operations inside abdominal cavity, including perigastric devascularization, lymph node dissection, and blood vessel ligation, must be performed using laparoscopic instruments. While, gastrectomy and digestive tract reconstruction could be completed with open approach through auxiliary incision (≤10 cm).

**Table 1 Tab1:** D1+/D2–10 lymphadenectomy

Lymph nodes	Non-Cardia GC		EGJA	
	cT1N0	cT1N1/cT2N0	cT1N0/cT1N1	cT2N0
No. 1	✔	✔	✔	✔
No. 2	✔	✔	✔	✔
No. 3	✔	✔	✔	✔
No. 4	✔	✔		
No. 5	✔	✔		
No. 6	✔	✔		
No. 7	✔	✔	✔	✔
No. 8a	✔	✔		✔
No. 9	✔	✔		✔
No. 10				
No. 11p	✔	✔		✔
No. 11d		✔		✔
No. 12a		✔		
No. 19				✔
No. 20				✔

*GC* Gastric cancer, *EGJA* Esophagogastric junctional adenocarcinoma

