### Sample size calculation

This is a non-inferiority verification study on clinical safety, with the early operative morbidity and mortality rate as the main index for safety evaluation. According to the previous reports, the morbidity and mortality rate for OTG is about 20%. Setting α=0.05, β = 0.2, and the noninferiority margin δ = 10%, the sample size required for each group is 90 cases. Considering that the maximum dropout rate for this clinical study is about 10%, the sample size is determined as 100 cases in each group.

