#### Exclusion criteria

Preoperative examinations indicate that the stage of the disease is clinical stage II/III/IV;Preoperative examination indicate enlargement of perigastric or retroperitoneal lymph nodes (min diameter ≥ 1.0 cm);Women during pregnancy or breast-feeding;Synchronous or metachronous (within 5 years) malignancies;Body temperature ≥ 38 °C before surgery or infectious disease with a systemic therapy indicated;Severe mental disease;Severe respiratory disease;Severe hepatic and renal dysfunction;Unstable angina pectoris or history of myocardial infarction within 6 months;History of cerebral infarction or cerebral hemorrhage within 6 months;Continuous systemic steroid therapy within 1 month (except for topical use);Gastric cancer complications (bleeding, perforation, obstruction) that requiring emergency surgery;Patients are participating or have participated in another clinical trial (within 6 months).

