### Randomized grouping

In this study, the central dynamic, stratified randomization method is adopted, and the factors including age, gender, BMI, and investigators, are considered. After each case is enrolled, the research center will arrange the research assistant to send the information of included cases (age, gender, and BMI) to the data center. After analyzing the case information by the center randomization department, the case grouping will be determined.

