#### Open total gastrectomy

The open total gastrectomy is similar to that of laparoscopic surgery, with the exception of operation performed under direct view.

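### Randomised patients found at operation to have stage II or higher disease are removed from the study, so the primary comparison depends on a judgement made after randomisation by a surgeon who knows the arm

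*Protocol article*

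**What the plan says.** All places are in the protocol article.

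- **Allocation.** Randomized grouping puts the request for allocation at enrolment: "After each case is enrolled, the research center will arrange the research assistant to send the information of included cases" to the data centre, which then assigns the group. The data sent are age, gender and BMI, and investigator is also a factor. Nothing found at operation enters into it.
- **Staging at operation.** Laparoscopic total gastrectomy has the abdomen entered and cytology taken, after which "the surgeon should explore the abdominal cavity to determine if there is any regional invasion or distant metastasis".
- **The rule.** The same section continues that, where stage II or higher disease is found during the operation, "D2 radical gastrectomy should be performed, and these patients will be excluded from this study".
- **The open arm.** Open total gastrectomy reads: "The open total gastrectomy is similar to that of laparoscopic surgery, with the exception of operation performed under direct view". The rule is thus carried over by similarity, with a different means of seeing.
- **Preoperative stage.** Exclusion criteria has a separate item: "Preoperative examinations indicate that the stage of the disease is clinical stage II/III/IV". It acts before allocation and is not at issue.
- **Endpoint.** Primary endpoint counts intraoperative haemorrhage of at least 400 ml, injury, pneumoperitoneum- and anaesthesia-related events, death during or after surgery, and complications to day 30.
- **Design and analysis.** Study design calls the trial open and non-inferiority. Sample size calculation sets a 10-point margin. Statistical analysis uses Newcombe 95% intervals for the difference and names no analysis set that would bring the excluded patients back.

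**The concern.** Randomisation protects the comparison only if the patients analysed are those who were randomised, or if any removal cannot depend on the arm. Here the removal is decided during the allocated operation, by the person performing it, who knows the arm. The two arms look for upstaging by different means, so they may not find it equally often or in the same kind of patient.

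The patients removed plausibly have a higher complication risk, and they still undergo a D2 gastrectomy. Any endpoint event before the decision, and any in the following 30 days, falls outside the comparison if the rule is followed as written. In a safety trial those are the events of interest.

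The objective and the eligibility criteria are framed by clinical stage I. A surgeon choosing between the two approaches before operation cannot know who will be upstaged, so these patients belong to the population about which the decision is made.

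**Working it through.** **1. Order of events.** Enrolment, then central allocation, then entry by the allocated route, then cytology and exploration, then the stage decision, then possible exclusion. That allocation precedes surgery is inferred from Randomized grouping and Laparoscopic total gastrectomy read together. No passage suggests another order.

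**2. Size of a spurious difference when detection is unequal.** The documents give no upstaging rate, no detection rate and no event risk by stage, so every input here is an assumption. There is no true difference between arms. Let s be the share truly stage II or higher, d the share of those detected and excluded, rU the event risk in upstaged patients and r0 the risk in the others. The event rate among patients retained in an arm is

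[(1 − s)·r0 + s·(1 − d)·rU] / [(1 − s) + s·(1 − d)].

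| s | rU / r0 | Detection, arm A v arm B | Retained rates, A v B | Difference |
|---|---|---|---|---|
| 5% | 35% / 20% | 70% v 50% | 20.2% v 20.4% | 0.2 points |
| 5% | 40% / 18% | 80% v 40% | 18.2% v 18.7% | 0.4 points |
| 15% | 35% / 20% | 80% v 40% | 20.5% v 21.4% | 0.9 points |
| 20% | 40% / 18% | 70% v 50% | 19.5% v 20.4% | 0.9 points |
| 20% | 40% / 18% | 80% v 40% | 19.0% v 20.9% | 1.8 points |

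Example, last row: arm A = (0.80×0.18 + 0.20×0.20×0.40)/(0.80 + 0.20×0.20) = 0.160/0.84 = 19.0%; arm B = (0.144 + 0.20×0.60×0.40)/(0.80 + 0.20×0.60) = 0.192/0.92 = 20.9%.

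The sign depends on which arm detects more. With equal d and equal risks the two rates are identical and the difference is zero.

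**3. Can discarded events change the conclusion?** This uses the plan's own method (Newcombe 95% interval, LTG minus OTG) and its 10-point margin. The upper limit is D + √[(u1 − p1)² + (p2 − l2)²], where D = p1 − p2, arm 1 is LTG, arm 2 is OTG, and l and u are the Wilson limits. The counts are hypothetical.

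- All randomised, 20/100 v 20/100: D = 0, u1 = 28.88%, l2 = 13.34%. Upper limit = √(8.88² + 6.66²) = 11.1 points. Non-inferiority is not shown.
- Drop 10 per arm, carrying 4 LTG events and 1 OTG event, leaving 16/90 v 19/90: p1 = 17.78%, u1 = 26.94%, p2 = 21.11%, l2 = 13.95%. Upper limit = −3.33 + √(9.16² + 7.16²) = 8.3 points. Non-inferiority is declared.

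A net imbalance of three discarded events reverses the conclusion.

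**4. Dropout allowance.** The plan's own step reproduces: 90/(1 − 0.10) = 100 per group. Whether 90 is itself enough is a separate question. Expected exclusions per 100 are 100·s·d. At s = 5% and d = 40-80% that is 2-4; at s = 20% it is 8-16. The first uses part of the 10 patients allowed for, and the second could use all of them.

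**The case against.** The strongest case against runs as follows.

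- **Bias needs unequal detection or unequal risk among those excluded.** The only textual sign of unequal detection is that open surgery is done under direct view; the procedure is otherwise carried across. This stands: the documents do not show that bias occurs, or in which direction.
- **The shift is small.** At most 1.8 points in the table, against a standard error of about 6 points at 90 per arm and a 20% rate: √(2×0.20×0.80/90) = 0.060. The entry criteria also select against advanced disease, so low upstaging is plausible. This stands as well, and is why the range starts at 5%.
- **The count example is chosen.** It drops equal numbers per arm, and 4 v 1 events could arise by chance. True. It shows how sensitive the conclusion is to a few discarded events, not what is likely.
- **Exploration comes before dissection, and follow-up covers both groups for 30 days.** Few surgical events may precede the decision, and events in excluded patients might still be recorded. Recording them would not help if the patients are out of the study, and most of their 30-day risk lies after the decision.
- **Excluded patients receive D2, not the D1+/D2-10 operation under study.** This is a reason for a supportive analysis without them, not for removing them from every analysis.

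Three stronger readings are tempting. A reader might infer that the rule favours LTG, but nothing in the text gives a direction. A reader might infer that the exclusions exhaust the dropout allowance, but no upstaging rate is given, and the article does not define dropout, so the 10% may have been meant to cover them. A reader might also infer that the article lacks rules on conversions or on agreement between analysis sets, but those are usual content of an analysis plan that is not shown.

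**Conclusion.** The point holds on the text. This is an explicit rule, not a detail left to another document, and an analysis plan that kept these patients would contradict it. Followed as written, it makes the primary comparison depend on an unblinded judgement made after randomisation, and it leaves out intraoperative and 30-day events that the endpoint definition counts.

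Confidence is high about the rule and low about its effect. Under the assumed inputs the spurious difference is about 0.2-1.8 points in either direction, and zero in expectation if detection and event risk among those excluded are equal across arms. Results near the margin can be reversed by a handful of discarded events. If upstaging is common, the exclusions may also use part or all of the 10% dropout allowance.

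**What to change.** Leave the surgical management of these patients as it is and change only their place in the study. In Laparoscopic total gastrectomy, and by extension the open arm, replace the clause that excludes them with: *will be followed to day 30 and included, in the arm to which they were randomised, in the primary analysis of all randomised patients who undergo surgery.*

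Give the analysis without upstaged patients as supportive only. Report the number of upstaged patients and their endpoint events by arm.

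The cost is a change of wording and a 30-day record for patients already under care; the article already plans 30-day follow-up in both groups. The downside is a slightly more heterogeneous primary population, including some patients who had D2 instead of D1+/D2-10 dissection.

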#### Open total gastrectomy

The open total gastrectomy is similar to that of laparoscopic surgery, with the exception of operation performed under direct view.

### Postoperative care

The surgeons and resident doctors will evaluate the patients twice a day for whether there are events that affect the patients’ recovery course. The time to first ambulation and flatus, etc. will be recorded until discharged. Laboratory findings are recorded on the first, third, and fifth postoperative day.

Continuous intravenous postoperative analgesia is allowable but not mandatory within 72 h postoperatively. Its dose, type, and rate of infusion should be performed according to clinical routines and patient conditions. The repeated use of prophylactic analgesic is not permitted 72 h after surgery unless it must be used.

Postoperative fluid infusion (including glucose, insulin, electrolytes, vitamins etc.) or nutritional support (enteral/parenteral) is performed according to the clinical routines. After oral feeding, it should stop or gradually reduce fluid infusion/nutritional support.

A patient can be arranged for discharge when meet the following requirements: no postoperative complications, body temperature is less than 37 °C, the pain can be tolerated, and more than 1/3 normal diet can be oral intake.

### Quality control

To ensure the rationality of the surgical procedure, the quality of lymphadenectomy, the length of incision, and the integrity of specimen, a series of photographs of surgery (LTG and OTC) are taken for assessment. All photographs will be saved and submitted to CLASS data center within 1 week after the operation. The CLASS Research Committee will monitor and review regularly to ensure the quality of operation.

### Outcome measurements

#### Primary endpoint

The primary endpoint of the CLASS02–01 trial is noninferiority in the early operative morbidity and mortality, which are defined as the event observed within 30 days following surgery. The postoperative complications are defined and graded according to the grading system of Clavien-Dindo Classification. To measure this endpoint, the criteria are suggested in details as follows:Intraoperative complicationsSurgery-related complications: intraoperative hemorrhage (≥400 ml) and injury;Pneumoperitoneum-related complications: hypercapnia, mediastinal emphysema, subcutaneous emphysema, aeroembolism, and respiratory and circulatory instability caused by pneumoperitonum;Anesthesia-related complication.Early postoperative complicationsSurgery-related complications: wound complications (infection, effusion, dehiscence, poor healing), intra-abdominal active bleeding, digestive tract active bleeding, anastomotic stenosis, intestinal fistula, pancreatic fistula, chylous fistula, intra-abdominal abscess formation, gastroparesis, intestinal paralysis, intestinal obstruction, cholecystitis, pancreatitis, etc.System-related complications: pneumonia, pleural effusion, pulmonary embolism, cardio-cerebrovascular complications, deep venous thrombosis, urinary tract complications, catheter-related complications, condition of pain, etc.;Intraoperative or postoperative death

#### Secondary endpoint

The secondary endpoint of this study is the postoperative recovery course, which is assessed by time to first ambulation, flatus, liquid diet, soft diet, etc. In addition, the length of postoperative hospital stay will be recorded.

### Follow-up

The patients in both groups will be followed up 30 days after operation. A physical examination, a complete blood count, blood biochemical examination (albumin, prealbumin, total bilirubin, direct bilirubin, AST, ALT, creatinine, blood urea nitrogen, and blood glucose), and serum tumor markers (AFP, CEA, CA19–9, CA12–5, and CA72–4) analyses will be performed. In addition, imageological examination (total abdominal and pelvic enhanced CT, chest X-ray, upper gastrointestinal tract iodine imaging, gastroscopy, ultrasonography, whole body bone scan, PET-CT, etc.) will also be performed if needed. All the results will be recorded and evaluated by the specialist.

### Statistical analysis

Statistical analysis will be performed with SAS Software (version 9.3; SAS Institute, Cary, NC). The data are presented as the mean ± standard deviation for continuous variables and as a number for categorical variables. The statistical significance will be evaluated using χ^2^ test, Fisher’s exact test, t test, or rank sum test. The Newcombe’s method will be used to compare the 95% CIs (confidence intervals) for between-group differences of intraoperative and postoperative morbidity and mortality. All *P* values were two sided, and differences were considered significant at values of *P* < 0.05.

## Discussion

Incidence of adenocarcinoma at the upper third of the stomach has increased over the past two decades in Western countries [14], and in Asian countries, such as Japan, Korea, and China, an increasing trend of proximal gastric cancer is also observed during the past years [15]. For gastric cancer located on the proximal side of the stomach, both proximal gastrectomy (PG) and total gastrectomy (TG) can be considered, and each has advantages and disadvantages [16]. PG could offer the functional benefits relative to TG, such as less dumping syndrome, improved postoperative nutrition, and decreased likelihood of anemia. While, severe esophageal reflux is a potential postoperative complication for PG, even in need of second operation and reconstruction of the digestive tract [16]. Till now, various reconstruction methods have been developed to prevent postoperative esophageal reflux following PG, such as double tract reconstruction and jejunal interposition, however, the anti-reflux effect is uncertain [17]. So in this clinical trial, to maintain the nutritional status and quality of life of the patients, we recommended TG and Roux-en-Y reconstruction of the digestive tract, which remains the easiest solution with satisfactory functional results [16]. In addition, the role of complete resection of No. 10 nodes has long been controversial and one retrospective study in China proved that complete clearance of No. 10 nodes is no need for proximal gastric cancer with early stage [18], so in this clinical trial, the resection of No. 10 nodes is not required.

This CLASS02–01 trial is the first prospective randomized two-arm controlled study to determine the safety of LTG compared with OTG. Close-out will occur July 2018, at which time data will be analyzed. The findings from this study will contribute to evidence-based information about the safety of LTG with lymphadenectomy for gastric cancer. After safety assessment of the CLASS02–01 trial, the following clinical trial (CLASS02–02) will compare the long-term survival outcomes between LTG and OTG. Through these clinical trials, we hope to show that LTG with lymphadenectomy for gastric cancer is safe and feasible.

## Abbreviations

AFP: Alpha fetal protein
ALT: Alanine aminotransferase
ASA: American society of anesthesiologists
AST: Aspartate aminotransferase
BMI: Body mass index
CA: Carbohydrate antigen
CEA: Carcinoembryonic antigen
CLASS: Chinese laparoscopic gastrointestinal surgery study group
CT: Computed tomography
DSMC: Data and safety monitoring committee
ECOG: Eastern cooperative oncology group
EGJA: Esophagogastric junctional adenocarcinoma
GC: Gastric cancer
JCOG: Japan clinical oncology group
JLSSG: Japanese laparoscopic surgery study group
KLASS: Korean laparoscopic gastrointestinal surgery study group
LADG: Laparoscopic-assisted distal gastrectomy
LTG: Laparoscopic total gastrectomy
OTG: Open total gastrectomy
PET-CT: Positron emission tomography-computed tomography
PG: Proximal gastrectomy
RCT: Randomized controlled trial
TG: Total gastrectomy
